#### *Toxicity Management*

In the event of toxicity or intolerance to MVC in this study, subjects should be managed as in standard clinical practice. This may involve discontinuing MVC in some cases.

### 7.8 Storage and analysis of samples

Blood samples will be collected from patients at each study visit.

Routine biochemistry, haematology and virology testing will be performed through routine laboratory procedures. Samples will be delivered immediately within the internal courier system from the clinic room to the laboratory.

The following blood volumes will be required:

5mL gold top (SST) for LFTs, U+Es, lipids, phosphate, CK, and thyroid function

4mL EDTA for HbA1c

4mL EDTA for full blood count

5mL gold top (SST) for ferritin, copper, caeruloplasmin, alpha-1 antitrypsin, coeliac serology, and liver autoantibodies

2mL grey top (oxalate/fluoride) for glucose

2mL blue top (trisodium citrate) for INR

4mL EDTA for CD4/CD8 cell counts

5mL gold top (SST) for anti-HIV antibody/antigen, anti-HCV antibody, HCV antigen and HBsAg

8mL EDTA for HCV RNA

8mL EDTA for HIV RNA

8mL EDTA for HIV tropism

5mL gold top (SST) for ELF score (assays for TIMP-1, PIINP, HA) [*research bloods*]

For the ELF score, samples will be frozen at -80C and stored at site, as described in the Laboratory Manual, and at the end of the study, batched and couriered on dry ice to the Centre for Hepatology, University College London, and assayed for the three components noted above.

Blood for the tropism assay will be couriered from the pathology service to the relevant laboratory according to routine procedures.

Total maximum volume of blood for each visit is as below:

Screen 47mL, baseline 24mL, week 4 19mL, week 24 19mL, week 48 32mL, week 72 19mL, week 96 32mL, ETV 28mL

Total maximum volume of blood in the study will be: 192mL

No blood samples will be stored after they have been tested for the designated test, except for the viral serology and viral PCR blood samples; surplus samples from these specimens are, as a routine, stored on site for 2 years as part of clinical care for the purpose of retrospective viral testing, should this be required for the patient's subsequent care (eg HIV resistance testing).

Blood tubes for ELF score will be provided by the sponsor.

Samples will be appropriately labelled in accordance with the trial procedures to comply with the 1998 Data Protection Act. Biological samples collected from participants as part of this trial will be transported, stored, accessed and processed in accordance with national legislation relating to the use and storage of human tissue for research purposes and such activities shall at least meet the requirements as set out in the 2004 Human Tissue Act.

Refer to the study Laboratory Manual for further site specific instructions.

For the creatinine clearance value calculations: <https://www.mdcalc.com/creatinine-clearance-cockcroft-gault-equation> web based calculator should be used and the obtained value should be verified according to the patient's BMI.

## 7.9 End of trial

The end of the trial will be the 96 week visit of the last participant.

## 8 TRIAL MEDICATION

### 8.1 Name and description of investigational medicinal product(s)

#### Maraviroc (Celsentri)

This is a licensed drug indicated with other antiretroviral medications for treatment-experienced adults infected with only CCR5-tropic HIV-1. It is supplied as a film-coated tablet. The recommended dose is 150mg, 300mg or 600mg twice daily depending on interactions with co-administered antiretroviral therapy and other medicinal products. For individuals with a creatinine clearance of between 30 mL/min and 80 mL/min, who are also receiving concomitant CYP3A4 inhibitors, the dosing interval should be increased to 150mg once daily. (For full details, see Table in the Separate document: current 'Summary of product characteristics for maraviroc' )

Of note, the maraviroc dose does not vary according to concomitant nucleos(t)ide reverse transcriptase inhibitor use due to no significant interactions.

For commonly used non-nucleoside reverse transcriptase inhibitors (NNRTIs), protease inhibitors (PIs) and integrase strand transfer inhibitors (INSTIs), the dose of concomitant maraviroc is as follows:

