|--------------------------------------------|------------------------------------------------------------------------------------------------------------------------------------------------------------------------------|------------------------------------------------------------------------------------------------------------------------------------------------------------------------------------------------------------------------------------------------------------------------------------------------------------------------------------|
|                                            | 
Assessment of the effect of maraviroc on HIV parameters in people living with NAFLD
 
Assessment of quality of life measures in people living with HIV and NAFLD
 | 
Change in the mean CD4 count and in the % with an undetectable HIV VL at 48 and 96 weeks in individuals randomised to receiving MVC plus OBT versus OBT alone
 
Responses at 48 and 96 weeks in individuals randomised to receiving MVC plus OBT versus OBT alone on the CLDQ:NAFLD, SF-36 and WPAI-SHP questionnaires
 |
| Investigational Medicinal Product(s)       | Maraviroc                                                                                                                                                                    |                                                                                                                                                                                                                                                                                                                                    |
| Formulation, Dose, Route of Administration | Film-coated tablets; oral; dose dependent on interactions with co-prescribed medications (according to SmPC recommendations)                                                 |                                                                                                                                                                                                                                                                                                                                    |

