## 6.2 Exclusion criteria

- (1) Severe cardiovascular disease including known angina or history of myocardial infarction
- (2) History of postural hypotension, defined as a reduction in the systolic blood pressure of  $\geq 20$ mmHg after standing for at least one minute
- (3) Individuals previously exposed to MVC
- (4) HIV viral load detectable ( $\geq 50$  copies/ml). One blip (VL 50-200 copies/ml) within 6 months prior to screen is allowed.
- (5) Current HCV or HBV (HBcAb-positive, HBsAg-negative is permitted; anti-HCV Ab positive with HCV RNA or HCV antigen negative for  $\geq 6$  months following treatment or spontaneous clearance is permitted)
- (6) Other chronic liver disease including but not exclusively: cirrhosis, alcohol-related liver disease, autoimmune hepatitis, primary biliary cirrhosis, primary sclerosing cholangitis, haemochromatosis, Wilson's disease, alpha-1 antitrypsin deficiency, non-cirrhotic portal hypertension, drug-induced as deemed by a hepatologist  
Note: alcohol-related liver disease includes liver disease in the presence of excess alcohol intake as defined according to EASL guidelines 2016 (ie  $>20$ g/day or  $>17$  units/week for women and  $>30$ g/day or  $>26$  units/week for men).
- (7) ALT or AST  $> 5$ x the ULN (where ULN is defined as 41 IU/L)
- (8) Severe renal insufficiency (creatinine clearance  $< 30$  mL/min)
- (9) HIV-2 infection
- (10) Known allergy or intolerance to MVC or its constituents including hypersensitivity to peanuts or soya
- (11) If female, pregnancy or breastfeeding

(12) Individuals currently taking medications or herbal agents that are contraindicated with MVC including St John's Wort.

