#### **8.6 Dosage schedules**

Maraviroc will be taken by participants in Group A orally at a twice daily dosing schedule. The total quantity of drug will be determined according to interactions with other co-administered medications, including antiretrovirals, in line with SPC recommendations.

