#### **8.7 Dosage modifications**

Modification of the dose of maraviroc will not be undertaken except where indicated due to potential drug-drug interactions with concomitant medications. Where a participant initiates a new medication or discontinues an existing medication, the investigator or his/her delegate will confirm whether or not a drug drug interaction could occur and hence any dose modification of MVC.

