### 8.12 Name and description of each Non-Investigational Medicinal Product (NIMP)

All participants will be receiving an OBT at screen which may consist of any cART regimen which has achieved a sustained undetectable HIV VL.

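### Section 8.6 puts Group A on twice-daily maraviroc without exception, but 8.1 requires once daily when creatinine clearance is 30-80 mL/min with a CYP3A4 inhibitor; 8.7 is unclear on the same case

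*Protocol*

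**What the plan says.** Protocol 8.1 gives maraviroc at 150, 300 or 600 mg twice daily according to interacting drugs. It then sets a separate rule for creatinine clearance 30-80 mL/min combined with a CYP3A4 inhibitor: "the dosing interval should be increased to 150mg once daily". The lists that follow place ritonavir- and cobicistat-boosted regimens at 150 mg twice daily.

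Protocol 8.6 states: "Maraviroc will be taken by participants in Group A orally at a twice daily dosing schedule". Its next sentence adds: "The total quantity of drug will be determined according to interactions with other co-administered medications, including antiretrovirals, in line with SPC recommendations".

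Protocol 8.7 states: "Modification of the dose of maraviroc will not be undertaken except where indicated due to potential drug-drug interactions with concomitant medications". It then describes one occasion for reviewing the dose: "Where a participant initiates a new medication or discontinues an existing medication".

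On eligibility, 6.2 item 8 excludes "Severe renal insufficiency (creatinine clearance" below 30 mL/min). Section 8.12 describes the background regimen as one "which may consist of any cART regimen which has achieved a sustained undetectable HIV VL". The trial summary gives the dose as "dose dependent on interactions with co-prescribed medications (according to SmPC recommendations").

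**The concern.** The sections headed for dosage schedule and dosage modification should agree with the section that fixes the dose. For one eligible subgroup they do not. Section 8.1 requires once-daily dosing, while 8.6 prescribes twice-daily dosing for the whole maraviroc arm. Someone checking the schedule in 8.6 finds no sign that an exception exists. Someone checking 8.7 when renal function declines finds no instruction to look again at the dose.

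What is at stake is the daily dose in participants with reduced clearance who also take an inhibitor, over a treatment period of 96 weeks in which renal function may change. Section 9.7 defines overdose as more than 1200 mg/day, so a doubled dose of 300 mg/day would not be picked up by that route.

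**Working it through.** The protocol gives no statistical figure to reproduce here. The check compares sections, with one line of arithmetic.

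1. **Is the subgroup eligible?** Yes. Only clearance below 30 mL/min is excluded (6.2 item 8), so 30-80 mL/min is admitted. Any suppressive regimen is allowed (8.12). Boosted regimens have their own dose list in 8.1, and protease inhibitor exposure is a stratification factor (sections 4 and 7.3). Both conditions of the 8.1 rule can therefore hold in one participant.

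2. **8.1 against 8.6.** Section 8.1 requires once daily for this participant; 8.6 says twice daily. The SPC reference in 8.6 qualifies the total quantity of drug, as determined by interactions. It mentions neither frequency nor renal function. The two regimens cannot both be followed.

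3. **Size of the difference**, for a participant on a boosted regimen:
   - 8.1 renal rule: 150 mg x 1 = 150 mg/day
   - 8.6 schedule with the 150 mg twice-daily list: 150 mg x 2 = 300 mg/day
   - Ratio: 300 / 150 = 2

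4. **8.1 against 8.7.** Two cases need separating.
   - Clearance is already 30-80 mL/min and an inhibitor is started. A medication has changed and an interaction arises, so 8.7 covers it and agrees with 8.1.
   - The participant is on a stable inhibitor and clearance falls to 80 mL/min or below. No medication has changed, so the prompt described in 8.7 does not arise, although 8.1 now requires a different dose. The general permission in 8.7 may still cover the change, because the 8.1 rule applies only alongside an interacting drug. The text does not settle this.

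5. **Could the second case be seen during the trial?** Yes. Creatinine is part of routine chemistry at baseline and weeks 4, 24, 48, 72 and 96 (Table 1, footnote 8), and 7.8 names a calculator for clearance. Section 7.8 does not say when clearance is to be recalculated and does not link the result to dose.

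**The case against.** The strongest reply is that no prescriber could take a wrong dose from 8.6 or 8.7 alone, because neither contains a milligram figure. To find any dose, the prescriber must open 8.1 or the SPC. In 8.1 the renal rule stands just before the 150 mg twice-daily list. The trial summary, 2.1, 8.1 and 8.6 all defer to the SPC, and a specific renal rule would naturally be read as qualifying a general schedule. This stands, and it makes an actual error unlikely. It does not remove the unqualified twice-daily statement in 8.6.

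Three stronger readings are tempting, and the documents do not support them:

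- *That 8.7 flatly forbids the 8.1 dose.* The 8.1 rule depends on a concomitant inhibitor, so it can fairly be treated as an interaction-related change. Section 8.7 does not say that starting or stopping a medication is the only occasion for review. Ambiguity is as far as the text goes.
- *That affected participants would accumulate a large excess up to week 96.* That assumes both 8.1 and the SPC are disregarded throughout. Nothing in the protocol suggests this, and the excess is zero if either is followed.
- *That the renal rule is missing.* It is stated in 8.1.

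**Conclusion.** The inconsistency between 8.1 and 8.6 is real: once daily against an unqualified twice daily for an eligible subgroup, or 150 against 300 mg/day at the dose listed for boosted regimens. Section 8.7 adds an ambiguity confined to clearance that falls while the inhibitor is unchanged.

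This is a minor-to-moderate dosing-safety inconsistency. It does not touch the sample size, the feasibility outcomes or the planned comparisons.

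The factor of 2 assumes that the ritonavir- and cobicistat-boosted regimens in the 150 mg twice-daily list count as CYP3A4 inhibitors. The protocol does not say so expressly, although 8.1 plainly foresees participants on such inhibitors. How many participants would be affected cannot be derived from the protocol.

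**What to change.** Keep 8.1 as the governing rule and align the other two sections with it.

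- In 8.6, after the twice-daily statement, add: *except 150 mg once daily where creatinine clearance is 30-80 mL/min with a concomitant CYP3A4 inhibitor (see 8.1 and the current SPC)*.
- In 8.7, add to the permitted reasons: *or where a change in creatinine clearance means a different dose applies under 8.1 or the SPC*.

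The cost is two short additions in a protocol amendment.

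A sensible option, not needed to remove the inconsistency, is to recalculate clearance at dispensing visits for Group A participants on an inhibitor. Drug is dispensed at baseline and weeks 4, 24, 48 and 72, and creatinine is already measured at each, so no extra blood is required. Weight is not taken at week 4, so the baseline weight would serve there. If all 30 planned Group A participants were on an inhibitor, the ceiling would be 30 x 4 = 120 post-baseline calculations.

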#### Maraviroc 150mg BD

|                                                 |                       |                       |                        |
|-------------------------------------------------|-----------------------|-----------------------|------------------------|
| Darunavir/ritonavir,
Elvitegravir/cobicistat | Atazanavir/ritonavir, | Darunavir/cobicistat, | Atazanavir/cobicistat, |
|-------------------------------------------------|-----------------------|-----------------------|------------------------|

#### Maraviroc 300mg BD

Rilpivirine, Nevirapine  
Raltegravir, Dolutegravir

#### Maraviroc 600mg BD

Efavirenz, Etravirine (in absence of a boosted PI) [note that Etravirine is only approved for use with a boosted protease inhibitor in the EU SPC]

### 8.2 Legal status of the drug

Maraviroc is licensed in the UK to be administered with other antiretroviral medications for treatment-experienced adults infected with only CCR5-tropic HIV-1.

### 8.3 Summary of Product Characteristics (SPC)

See separate RSI review document and the current version of 'Summary of Product Characteristics for Maraviroc'

#### **8.4 Drug storage and supply**

The trials pharmacy will maintain its own stock and will be responsible for ordering further IMP when necessary. The trials pharmacy will maintain accountability logs and ensure prescriptions are signed only by a medically-qualified doctor listed on the delegation log.

#### **8.5 Preparation and labelling of Investigational Medicinal Product**

IMP will be delivered to the Royal Free Hospital from the manufacturer where the QP process will be performed, including the labelling, release activity and QP certification. The labelled IMP will then be couriered to the clinical trials pharmacy. The first supply will be triggered once the first participant is screened.

#### **8.6 Dosage schedules**

Maraviroc will be taken by participants in Group A orally at a twice daily dosing schedule. The total quantity of drug will be determined according to interactions with other co-administered medications, including antiretrovirals, in line with SPC recommendations.

#### **8.7 Dosage modifications**

Modification of the dose of maraviroc will not be undertaken except where indicated due to potential drug-drug interactions with concomitant medications. Where a participant initiates a new medication or discontinues an existing medication, the investigator or his/her delegate will confirm whether or not a drug drug interaction could occur and hence any dose modification of MVC.

#### **8.8 Known drug reactions and interaction with other therapies**

Please see the current Summary of Product Characteristics for Maraviroc for known drug interactions

#### **8.9 Concomitant medication**

Please see the current Summary of Product Characteristics for Maraviroc for known drug interactions with respect to contraindicated medications.

#### **8.10 Trial restrictions**

For women of child bearing potential, contraception needs to be used for the duration of the study. This includes the following, according to the woman's preference and DDIs with concomitant medications:

- Intrauterine Device (IUD)

- Hormonal based contraception (pill, contraceptive injection, implant, IUS etc.)
- Double Barrier contraception (condom and occlusive cap e.g. diaphragm or cervical cap with spermicide)
- True abstinence

### 8.11 Assessment of compliance

Aim: To describe how compliance will be assessed

Participant adherence to MVC will be assessed through:

- a) Self reporting of doses of MVC taken via a diary card
- b) Pill counting at each visit by a pharmacist/research team member and recording of the number of pills returned

Participants will bring in all pill bottles at each study visit. The total number of IMP pills remaining at each visit will be counted and, then returned to the participant to take until the bottle is finished.

The percentage of IMP compliance for each participant will be calculated. Where this figure is <80%, this will lead to likely withdrawal from the study although this will be at the discretion of the PI. Where a discrepancy exists between self reported compliance and compliance identified via pill counting, any decision to withdraw the participant will rest with the study PI.

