| Trial Participants                 | People living with well-controlled HIV-1 and non-alcoholic fatty liver disease                                                                                                                                       |                                                                                                                                                                                                                                                                                                                                                                                                                                                                                                                                                                                           |
| Planned Sample Size                | Total number n=60                                                                                                                                                                                                    |                                                                                                                                                                                                                                                                                                                                                                                                                                                                                                                                                                                           |
| Treatment duration                 | 96 weeks                                                                                                                                                                                                             |                                                                                                                                                                                                                                                                                                                                                                                                                                                                                                                                                                                           |

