## 7.6 Trial assessments

Please see Table 1 for details of the timeline for trial visits and which procedures and assessments will be performed at each visit.

The following are recorded at the baseline visit and then every 24 weeks until the final visit at 96 weeks (i.e. day 1, week 24, week 48, week 72 and week 96):

- history and if necessary symptom-directed examination
- adherence to maraviroc as assessed by (i) self reported adherence through completion of a diary card and (ii) pill counting by pharmacy/research team member.
- weight and BMI
- waist circumference
- liver function, renal function, phosphate, CK, glucose (fasted at baseline, weeks 48 and 96), and lipid profile (fasted at baseline, weeks 48 and 96)(blood draw)
- FBC (blood draw)
- HIV viral load (blood draw)
- Urine dipstick macroanalysis and, for WOCBP, pregnancy testing

The following are recorded at the baseline visit and then every 48 weeks until the final visit at 96 weeks (i.e. day 1, week 48 and week 96):

- CD4/CD8 cell count and % (blood draw)
- HbA1c (blood draw)
- ELF score (blood draw)
- CLDQ:NAFLD questionnaire
- SF-36 questionnaire
- WPAI-SHP questionnaire
- Dietary and exercise history

The following is recorded at screen, week 48 and week 96:

- Fibroscan. For screening, the Fibroscan may be performed up to 42 days prior to baseline. For the week 48 and 96 visits this may be performed within 7 days of the study visit.

The following **optional investigation** will be performed at the baseline visit and at the 96 week visit:

- CT liver : spleen attenuation ratio. This may be performed within 7 days of the study visit with preference for the 7 days prior to baseline.

An additional week 4 safety visit will be required for those individuals in the maraviroc group, with the following procedures being performed:

- assessment of any drug toxicity through targeted history and, if required, examination
- liver function, renal function, CK, phosphate, glucose, full blood count (blood draw)
- HIV viral load (blood draw)

The following will be performed at screening only (if no hepatic imaging or liver biopsy result is available in the preceding 24 weeks):

- USS liver

The following will be performed at baseline only (if not available in the preceding 24 weeks):

- CCR5 tropism (blood draw)

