### **Early termination visit**

Those individuals who withdraw from the study early will be requested to attend an early termination visit, during which the following assessments will be performed:

- history and examination
- adherence to maraviroc as assessed by (i) self reported adherence and (ii) pill counting by pharmacy/research team member.
- weight and BMI
- waist circumference
- liver function, renal function, CK, phosphate, fasting glucose, HbA1c and fasting lipid profile (blood draw)
- FBC (blood draw)
- HIV viral load (blood draw)
- ELF score (blood draw)
- Urine dipstick for macroanalysis and, for WOCBP, pregnancy testing
- CLDQ:NAFLD questionnaire
- SF-36 questionnaire

- WPAI-SHP questionnaire
- Dietary and exercise history
- Fibroscan

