### 7.7 Withdrawal criteria

A subject is free to withdraw from the study at any time. In addition, the Investigator may decide, for reasons of medical prudence, to withdraw a subject. If a subject discontinues study medication dosing, every attempt should be made to keep the subject in the study and continue to perform the required study-related procedures and follow-up procedures. If this is not possible or acceptable to the subject or Investigator, the subject may be withdrawn from the study.

Study medication may also be discontinued in the following instances:

1. If the subject withdraws his/her consent.
2. If the investigator considers in the interest of the subject (i.e. intercurrent illness, unacceptable toxicity) that it is best for them to withdraw their consent.
3. The subject fails to comply with the protocol requirements or fails to cooperate with the investigator.
4. Pregnancy during the course of the study.

The date and reasons for the withdrawal will be clearly stated on the subject's eCRF and source document. Every attempt should be made to arrange follow up visits for subjects who are withdrawn from the trial (including where individuals fall pregnant).

Subjects withdrawing from the trial may be replaced if considered necessary by the Chief Investigator.

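### Section 8.11 hands leftover maraviroc back at every visit to be finished, with no exception for week 96 or for participants whose study drug has been stopped

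*Protocol*

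**What the plan says.** Section 8.11 (Assessment of compliance) has participants bring all their bottles to every study visit. Maraviroc "pills remaining at each visit will be counted and, then returned to the participant to take until the bottle is finished". No visit is excepted.

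The visits at which this happens are set elsewhere:

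- Section 7.6 introduces its first list with "The following are recorded at the baseline visit and then every 24 weeks until the final visit at 96 weeks", and that list includes "self reported adherence through completion of a diary card and (ii) pill counting by pharmacy/research team member". Week 96 is therefore a pill-count visit.
- The early termination visit is described as follows: "Those individuals who withdraw from the study early will be requested to attend an early termination visit". Its assessments include "self reported adherence and (ii) pill counting by pharmacy/research team member".

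The provisions on when drug stops are these:

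- The Trial Summary row "Treatment duration" gives 96 weeks.
- Section 13.10 says participants are told at consent that maraviroc ends with the trial. Requests to continue are considered case by case by the local HIV team.
- Section 7.7 opens a list with "Study medication may also be discontinued in the following instances". The list covers withdrawn consent, the participant's interest ("intercurrent illness, unacceptable toxicity"), failure to comply, and pregnancy.
- Table 1 marks drug dispensation at baseline and weeks 4, 24, 48 and 72, and leaves it blank at week 96 and early termination.

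Section 8.4 makes the trials pharmacy keep accountability logs. It does not say what happens to tablets left at a participant's last visit.

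**The concern.** The return rule makes sense between visits, where a part-used bottle carries over to the next interval. Applied at the last visit, it sends the participant home with trial drug and an instruction to finish it, when the rest of the protocol says treatment is over.

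At stake is a small matter of participant safety and of protocol consistency. Week 96 and early termination are the last visits with scheduled haematology, chemistry and HIV viral load, so any further dosing would have no planned laboratory check behind it. Some of those leaving early may have had maraviroc stopped because it was not tolerated. Section 13.4 bars planned departures from the protocol. Yet at week 96, where continuation has not been agreed, a site that keeps the tablets departs from 8.11 and a site that returns them departs from 13.10.

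**Working it through.** The protocol gives no figure to reproduce here. The check sets the provisions side by side.

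**Step 1. Does the return rule reach the last visits?** 8.11 applies at each visit. 7.6 schedules a pill count at week 96, and the early termination list schedules one there. Neither list, nor 7.7, 8.4 or 8.11, says that leftover tablets are kept. The rule as written reaches both visits.

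**Step 2. Week 96.**

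| Provision | Instruction at week 96 |
|---|---|
| 8.11 | Count leftover tablets, hand them back, participant finishes the bottle |
| Trial Summary | Treatment lasts 96 weeks |
| 13.10 | Maraviroc stops after the trial unless continuation is agreed individually |
| Table 1 | No dispensing |

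The first row cannot be followed together with the second and third, except for someone whose continuation has been agreed. The Table 1 row concerns new supply. It supports the intention to stop but is not itself contradicted by returning old stock.

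**Step 3. Early termination.** The conflict here is narrower. It arises for a participant whose study drug has been stopped under 7.7: 8.11 would return the tablets to someone who has been told not to take them. The same applies to a participant who stops drug but stays in follow-up, which 7.7 encourages, because 8.11 has no exception at later visits either.

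**Step 4. What follows if drug is taken afterwards?**

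- Outcomes: the pill count comes before the return, so the adherence data are unaffected. No trial outcome changes.
- Safety reporting under 9.3: routine adverse event reporting ends at the final study visit. Serious events stay reportable to 30 days after treatment stops, and later events judged related are still reported.
- Laboratory monitoring: none is scheduled.

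**Step 5. How much drug?** The protocol does not state the quantity dispensed at week 72, so the answer is unknown. As an illustration only, assume no stock carried over from earlier intervals.

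- Weeks 72 and 96 are 24 × 7 = 168 days apart, and each visit has a window of ±7 days. The interval is therefore 168 − 14 = 154 to 168 + 14 = 182 days.
- Days left at full adherence = max(0, supply − interval).
- Assumed supply of 168 days: 168 − 154 = 14 days left at the shortest interval, and 0 at 168 days or longer.
- Assumed supply of 182 days: 182 − 154 = 28 days left at the shortest interval, 14 at 168 days, and 0 at 182 days.
- Assumed supply of 168 days with on-time visits but incomplete adherence: 90% leaves 168 × 0.10 = 16.8, about 17 days; 80% leaves 168 × 0.20 = 33.6, about 34 days.

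The range runs from nothing to several weeks, and it depends wholly on assumptions the protocol does not supply.

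**Step 6. How many participants?** Section 10.1 plans 30 per group with 33% attrition, so 30 × 0.67 = 20.1, about 20 maraviroc participants, would reach week 96 on plan. How many of them would have tablets left is unknown. Of the remaining 30 × 0.33 = 9.9, about 10, the protocol says only that those who withdraw will be asked to attend an early termination visit. It gives no attendance figure and no figure for those who would bring tablets.

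**The case against.** The strongest reply is that the protocol, read as a whole, already stops the drug. The treatment duration, the empty dispensing cells in Table 1 and 13.10 all point the same way. The disputed sentence sits in a section on measuring compliance and does not purport to set how long treatment lasts. The visit wording is also loose: 7.6 lists maraviroc pill counting on day 1, before any dose has been taken. Most sites would keep the tablets, and pharmacy instructions that are not among the documents may cover final reconciliation.

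Much of this stands. The intention to stop is clear, and a site is unlikely to read a pill-count sentence as an order to resume a drug stopped for toxicity. What does not fall away is that 8.11 gives a positive instruction, and at these visits it is the wrong one. This is not a detail left to another document.

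Three stronger readings are tempting and should be resisted:

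- A reader might infer that 8.11 removes a poorly adherent participant and hands back the tablets in the same step. The text does not say so. Below 80% compliance, withdrawal is only likely and is left to the principal investigator. Where the participant stays on treatment, returning the tablets is correct.
- A reader might infer that every early termination visit produces a contradiction. Stopping drug and leaving the study are different events in 7.7, and some attendees will already have been off drug for some time with nothing left to return.
- A reader might conclude that the clause could affect all 30 maraviroc participants. That would need every dropout to attend an early termination visit with tablets left, and attrition can include people who never come back.

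**Conclusion.** The point holds as a minor error in a stated instruction. At week 96 the return rule in 8.11 contradicts the 96-week treatment duration and 13.10. At early termination it conflicts with 7.7, but only for participants whose study drug has been stopped. The practical effect is possible maraviroc use after the last scheduled safety bloods and HIV viral load. It is limited by the serious-event reporting period, which runs from the end of treatment, and by the local follow-up that 13.10 offers.

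Its size cannot be stated in participants or in days. The day ranges above are illustrations on assumed supplies and should not be quoted as findings. The conclusion itself rests only on the wording of the protocol and on the absence of an exception anywhere in it.

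**What to change.** Amend 8.11 in two respects. First, limit the return of counted tablets to visits after which study treatment continues. Second, state that at week 96, at early termination or on permanent discontinuation of maraviroc, all unused tablets are counted, retained by the site and entered in the pharmacy accountability log already required by 8.4. If continuation has been agreed under 13.10, supply would follow that decision and not the leftover trial stock.

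The cost is a sentence or two in one section. No visit, outcome, sample size or analysis changes.
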